**Active surveillance/ preemptive therapy group**

Subjects in this arm of the study will have serum drawn twice a week for BDG testing while in the SICU, with the results of the test reported to the managing clinicians in real-time. Subjects will receive intravenous (IV) anidulafungin should the β-D-glucan exceed 60 pg/ml on a single determination. A positive test cut-off of 60 pg/ml was selected based on the observation that 81% of patients with IC will have a positive test at this level(25). Preemptive therapy will continue for a minimum of 14 days or for as long as the subject remains in the ICU up to a maximum of 28 days duration.

If the BDG test turns positive and preemptive therapy is initiated, serum will then be collected every other day to assess the kinetics of the BDG test on anidulafungin treatment. Kinetic monitoring will continue until the test becomes negative at which time twice weekly assessments will be resumed and continue for as long as the patient remains in the SICU. Samples collected while patients are receiving anidulafungin will be batched and run retrospectively. Clinicians will not have these results made available for use in real-time. However, once preemptive anidulafungin therapy is completed and the drug has been stopped, biweekly monitoring with results reported to the medical team will be resumed. Subjects, however will not be restarted on anidulafungin should the test again turn positive after a course of preemptive therapy is completed.

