**END OF PREEMTPIVE THERAPY**

- Clinical response to therapy will be recorded on the CRF (**Table 5)**.
- Subjects will again be assessed for EORTC/MSG criteria for proven or probable IFI.
- Oral wash or ETS for semi-quantitative fungal culture with susceptibility testing.

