**Clinical Response**

Response to empiric therapy will be defined as the resolution of fever and/or other attributable symptoms or signs of IFI after the initiation of systemic antifungal treatment. Response to preemptive therapy will be defined as normalization of the BDG test and resolution of fever and/or other attributable symptoms or signs of IFI (if these were present at the time the BDG test became positive) after the initiation of anidulafungin treatment.

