**Statistical Analyses**

Statistical analysis will be performed using SAS software. P values and 95% confidence intervals will be 2-tailed and statistical significance set at the 5% level unless otherwise specified.

*Demographics and Baseline Characteristics*

Demographic and baseline characteristic information will be summarized and compared using the Chi-squared test for discrete variables and one way ANOVA for continuous various to assess any imbalance between treatment groups.

*β-D-glucan Test Characteristics*

β-D-glucan test characteristics, using data collected from standard care group, will be described using sensitivity, specificity, positive and negative predictive values. Proven and probable cases of IFI, as defined by EORTC/MSG criteria (**tables 3 and 4**), will constitute the standard for comparison.

*Feasibility Analysis*

Feasibility will be a description of preemptive protocol adherence, BDG test requests off schedule, and the number of patients withdrawn from the preemptive arm due to the initiation of empiric systemic antifungal therapy in the absence of a positive BDG test.

*Efficacy End-Points*

Development of IFI during the study period will be assessed by the principal investigator (PI) and a second blinded investigator using predefined EORTC/MSG criteria for proven or probable disease. The study period is defined as the time the patient was cared for in the SICU. The proportions of patients developing IFI, and IC specifically, in each group will be compared using Fisher’s exact test. The median ICU stay and number of febrile days while in the ICU will be compared using the Kruskal-Wallis test. Patient mortality, overall and attributed to IFI, will also be summarized by group. Response-to-therapy (RTT) will be determined by the PI and a blinded second investigator. The RTT population will consist of all patients who were underwent BDG monitoring for at least 3 days and received at least 1 dose of systemic antifungal therapy.

*RNA Analyses*

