**Data Analysis**

Data Analysis will be performed after completion of data entry, database closure, and verification of database accuracy. All primary and secondary analyses will be performed on the intent-to-treat basis.

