**Table 5. Clinical Response**

| **Clinical response*** | **Definition** |
| --- | --- |
| Response to empiric therapy | Resolution of fever and/or other attributable symptoms/signs of IFI |
| Response to preemptive therapy | Resolution of abnormal BDG test result |

*Clinical response as an efficacy endpoint will be assessed at the end of treatment.

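### Response to preemptive therapy has two definitions that disagree for symptomatic patients, and its BDG component needs results that are not available when sampling is to change or when response is recorded

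*Protocol*

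**What the plan says.** Clinical response is secondary objective 6 and secondary endpoint 6. It is defined in two places.

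- END POINT DEFINITIONS, Clinical Response, preemptive therapy: "Response to preemptive therapy will be defined as normalization of the BDG test and resolution of fever and/or other attributable symptoms". The sentence then limits the clinical part to patients who had such signs when the BDG test became positive.
- Table 5, preemptive therapy: "Resolution of abnormal BDG test result". There is no clinical part. The table's footnote places the assessment at the end of treatment.

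For empiric therapy the Clinical Response section says "Response to empiric therapy will be defined as the resolution of fever and/or other attributable symptoms or signs of IFI". Table 5 agrees, and neither place adds a BDG component.

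The procedures for the end of preemptive therapy state "Clinical response to therapy will be recorded on the CRF" and point to Table 5.

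On sampling, the Active surveillance/preemptive therapy group section says "Kinetic monitoring will continue until the test becomes negative at which time twice weekly assessments will be resumed" and, in the same paragraph, "Samples collected while patients are receiving anidulafungin will be batched and run retrospectively". Footnote d of the Chart of Study Procedures and the While on Preemptive Therapy section repeat the rule of sampling until negative. The footnote adds that these kinetic results do not go to clinicians. Real-time reporting resumes only after the drug has been stopped.

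**The concern.** Two problems meet in one endpoint.

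First, the section that defines response and the table that the case report form follows ask for different things, and nothing says which prevails. The same data can then yield two response rates, and the choice could be made after the data are seen.

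Second, both versions need a BDG result at moments when the protocol's own testing arrangement does not supply one: when sampling is to drop from every other day to twice weekly, and when response is entered at end of therapy. The response field might be left blank or filled from the clinical picture alone. The kinetic series might be shortened or prolonged differently from patient to patient, which would blur the time to clearance that it is meant to measure.

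**Working it through.** **Denominator.** The Sample Size section gives 75 patients under active surveillance and 25% expected to turn positive. 75 × 0.25 = 18.75, rounded up to 19. This reproduces the protocol's number expected to receive anidulafungin.

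**Where the definitions part.**

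| Signs at positive test | Signs at end of therapy | BDG at end of therapy | Clinical Response section | Table 5 |
| --- | --- | --- | --- | --- |
| No | any | cleared | responder | responder |
| Yes | resolved | cleared | responder | responder |
| Yes | persisting | cleared | non-responder | responder |
| any | any | not cleared | non-responder | non-responder |

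Only the third row differs.

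**How many patients this could move.** The protocol gives no rates for clearance or symptom resolution, so this is an illustration on assumed values. Let B be the probability that BDG normalizes, S the probability that signs resolve if present, and f the share with signs at the positive test. B and S are taken as independent.

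- Table 5: 19 × B
- Clinical Response section: 19 × B × (1 − f + f × S)
- Difference: 19 × B × f × (1 − S)

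With B = S = 0.6:

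- Table 5: 19 × 0.6 = 11.4
- Section, f = 0.25: 19 × 0.6 × 0.90 = 10.3
- Section, f = 0.50: 19 × 0.6 × 0.80 = 9.1
- Section, f = 1.00: 19 × 0.6 × 0.60 = 6.8

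With B and S each from 0.4 to 0.8 and f from 0.25 to 1.0, Table 5 gives 7.6 to 15.2 responders of 19 and the section gives 3.0 to 14.4. The difference runs from 19 × 0.4 × 0.25 × 0.2 = 0.4 patients to 19 × 0.8 × 1.0 × 0.6 = 9.1. If clearance and clinical resolution tend to occur together, the difference shrinks. It is zero if no treated patient has signs at the start, or if every symptomatic patient whose BDG clears also resolves clinically.

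**Information flow.** Sampling every second day over a 14 to 28 day course is about 14/2 = 7 to 28/2 = 14 samples, if no switch occurs. None has a reported result during therapy. The step down to twice weekly is triggered by one of those results, and the response entry at end of therapy needs one too. The Case Report Forms section asks for data entry within 24 hours of the evaluation, and the end-of-therapy procedures list no BDG draw.

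**The case against.** The best defence has three parts.

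- Hypothesis 1 expects BDG to detect infection before signs develop. If most treated patients have no signs at the positive test, the definitions nearly coincide. This stands and bounds the size, but the protocol does not say how many will be symptomatic.
- Table 5 could be shorthand. That is hard to sustain, because it is the table cited for the case report form.
- The batch run will eventually give the BDG results, and response is to be determined by the principal investigator and a blinded second investigator, which leaves room for later adjudication. This also stands in part: the endpoint is recoverable. But the protocol does not provide for that step, and the batch can date the first negative closely only if frequent sampling did not stop too soon.

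A reader might also infer stronger points that the protocol does not support.

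- *That a planned comparison between arms is invalid.* Objective 6 is to evaluate response, whereas several neighbouring objectives say compare, and no test is named for it. The unlike definitions call for caution in side-by-side reporting only.
- *That most responders will be false positives clearing on their own.* Taking 25% positivity and the cited 81% sensitivity, the false-positive share is 1 − prevalence × 0.81/0.25. At assumed invasive candidiasis (IC) prevalences of 5, 10, 15 and 20% this is 84, 68, 51 and 35%, so a majority exists only below 0.125/0.81 = 15.4%. The sum counts other fungal infections as false positives, and the protocol gives no clearance data.
- *That the response population breaks the intention-to-treat rule.* The set is patients who "underwent BDG monitoring for at least 3 days and received at least 1 dose of systemic antifungal therapy", while Data Analysis says "All primary and secondary analyses will be performed on the intent-to-treat basis". Response to treatment has no meaning in untreated patients, so a treated subset is unavoidable. The 3 days refer to monitoring, not to survival after the first dose.
- *That kinetic samples are tested only after the study.* End-of-study testing is stated for standard-care serum. No date is given for the on-treatment batches.

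**Conclusion.** The point holds in two limited parts. The two definitions of preemptive response contradict each other for patients who had signs at the positive test, still have them at end of therapy, and have a cleared BDG. The until-negative sampling rule and the end-of-therapy response entry both need results that retrospective batching does not supply in time.

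The effect on the reported rate cannot be fixed from the protocol. In the illustration it ranges from less than one to about nine of 19 patients, on assumed rates and independence. This is one of 12 secondary endpoints in a feasibility study that is not powered for efficacy. The correction should be made, but the study's main conclusions do not hang on it.

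**What to change.** - Make the Clinical Response section and Table 5 identical. The section's version, with its condition on signs at the positive test, gives every treated patient a definable result, including those without symptoms.
- Record the clinical component at end of therapy. Derive the BDG component afterwards from the batch results by a rule fixed in advance: which sample counts, what value is normal, and what happens if no sample lies near the end of therapy. Normalization has no stated value, and the positive threshold is worded as exceeding 60 pg/ml in one section and as ≥ 60 pg/mL in another; these need reconciling.
- Report the two components separately as well as together.
- State that the composite preemptive response is descriptive. Because empiric response is clinical only, allow only the clinical component, among patients with signs at the start of therapy, to be set beside the empiric arm.
- Reconcile the until-negative rule with retrospective batching wherever it appears, so that the sampling schedule does not depend on an unavailable result.

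The cost is wording, a split response field on the case report form and a short derivation rule. The number of kinetic draws may change, depending on how the sampling rule is reconciled. The preemptive response rate may also look lower than under Table 5.

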**ASSESSMENT OF SAFETY**

Safety will be assessed by adverse events (AEs), physical examination, measurement of vital signs, and through the use of clinical laboratory tests obtained either as a part of routine care or once weekly during active preemptive treatment.

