**Chart of Study Procedures**

| **Procedure** | **Screening/Baseline** | **Weekly** | **Bi-weekly** | **Treatment** | **SICU Discharge** |
| --- | --- | --- | --- | --- | --- |
| **Informed Consent** | **X** |  |  |  |  |
| **Clinical Information** | **X^a^** | **X^a^** |  |  |  |
| **Physical Examination** | **X** |  |  | **X^b^** |  |
| **APACHE II Score Assessment** | **X** |  |  | **X** |  |
| **IFI Assessment^c^** | **X** | **X** |  |  | **X** |
| **Medication Review** | **X** | **X** |  |  |  |
| **Β-D-Glucan^d^** | **X** |  | **X** | **X** |  |
| **Fungal Culture^e^** | **X** |  |  | **X** | **X** |
| **Fungal Susceptibility^e^** | **X** |  |  | **X** | **X** |
| **Β-hCG** | **X^f^** |  |  |  |  |
| **LFTs^g^** | **X** |  |  | **X** |  |
| **RNA collection^h^** | **X** |  | **X** | **X** |  |
| **Blood Culture^i^** |  |  |  | **X** |  |

^a^Demographics, baseline conditions, pertinent past medical history at baseline followed by weekly assessment for evidence of IFI and for IC risk factors.

^b^Obtain within 72 hours of 1^st^ dose of study drug and weekly there after while receiving anidulafungin.

^c^ Vital signs, clinical signs and symptoms, routine laboratory tests, culture results, radiographic findings, and/or biopsy reports indicative of IFI.

^d^ Only BDG results for subjects in the active surveillance/preemptive therapy arm will be reported to clinicians in real-time. BDG testing for subjects receiving usual care will be performed in batches, retrospectively. Subjects on anidulafungin will have the BDG test performed every other day until negative to determine kinetics on therapy. Samples collected for BDG kinetics will be batch tested retrospectively, therefore the results will not be reported to clinicians.

^e^ Oral swish and spit or ETS aspirate (from those subjects requiring mechanical ventilation) to assess for fungal colonization will be performed at baseline, after the completion of any systemic antifungal therapy, and at SICU discharge. Susceptibility testing to echinocandins and fluconazole will be performed on each isolate recovered. Results will not be reported to the care providers.

^f.^ Pregnant women will be excluded from the study.

^g^ LFTs will be collected at baseline and weekly on anidulafungin. LFTs include: total bilirubin, alkaline phosphatase, AST, and ALT

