**Screening/Baseline**

Procedures must be performed within 3 days prior to randomization:

- **Signed informed consent prior to the performance of any study-specific procedures.**
- Complete medical and medication history, including a prior antifungal therapy review.
- Complete physical examination including vital signs.
- Liver function tests will be drawn if not already done as a part of standard care in the preceding 3 days.
- Calculate APACHE II score (<http://www.sfar.org/scores2/apache22.html>)
- Oral wash or ETS for semi-quantitative fungal culture with susceptibility testing.
- B-HCG test for women of childbearing age if not already done as a part of standard care (<60 years old)

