**INITIATION OF PRE-EMPTIVE OR EMPIRIC THERAPY**

- APACHE II score recalculated based on laboratory and clinical features in preceding 24 hours (http://www.sfar.org/scores2/apache22.html).
- Complete physical examination including vital signs will be obtained within 72 hours of study drug initiation.
- Assess and document whether patient meets EORTC/MSG criteria for proven or probable IFI.
- Laboratory evaluation (LFTs will be obtained if not already done in preceding 3 days).
- Oral wash or ETS for semi-quantitative fungal culture with susceptibility testing will be performed.
- Supporting evidence of IFI obtained as part of routine care will be documented.
- Positive BDG test will prompt two sets of blood cultures to be obtained within 12 hours, if not already collected a part of routine care. Culture results will be made available for clinical care.
- Concomitant medications will be documented.
- AEs will be recorded.

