**WHILE ON PREEMPTIVE THERAPY**

- Serum for BDG will be collected every other day until negative. Once the test becomes negative, twice weekly surveillance will be resumed.
- Complete physical examination including vital signs once weekly.
- Assessment for breakthrough IFI as defined by EORTC/MSG criteria.
- LFTs once weekly.
- AEs will be recorded and drug tolerability assessed at the time of the physical examination.
- PAX Gene tubes will continue to be obtained 2 times/week.
- Concomitant medications will be documented weekly.

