**Safety**

All patients who receive at least 1 dose of study medication will be included in the safety analysis. The prevalence of treatment emergent adverse events will be described using summary statistics and compared used the Chi-square test.

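### After therapy starts, repeat liver tests and examinations are scheduled only on anidulafungin, so an adverse-event comparison with standard care is open to detection bias against the drug

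*Protocol*

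**What the plan says.** At baseline both arms are treated alike. Screening/Baseline asks for "Complete physical examination including vital signs" and states "Liver function tests will be drawn if not already done as a part of standard care in the preceding 3 days". The section on initiating pre-emptive or empiric therapy, whose heading covers both, asks for one further LFT set if none is recent.

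The schedules then part. Footnote g of the Chart of Study Procedures says "LFTs will be collected at baseline and weekly on anidulafungin". Footnote b places later examinations around the first dose of study drug and "weekly there after while receiving anidulafungin". The list for patients on preemptive therapy repeats both as weekly items and adds "AEs will be recorded and drug tolerability assessed at the time of the physical examination". The Empiric Therapy list has a weekly AE record but no repeat LFTs and no examination. The All Subjects list likewise has a weekly AE record and neither procedure. Assessment of Safety accepts laboratory tests from either source: "clinical laboratory tests obtained either as a part of routine care or once weekly during active preemptive treatment".

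The Safety paragraph says "The prevalence of treatment emergent adverse events will be described using summary statistics and compared used the Chi-square test". It does not name the groups, and it limits the safety set to patients who received study medication. The second synopsis aim sets the safety of preemptive anidulafungin against current practice. Safety and tolerability is one of three primary endpoints, and the Data Analysis paragraph puts all primary analyses on an intent-to-treat basis.

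**The concern.** An LFT abnormality enters the AE record only if someone draws the test. On anidulafungin the protocol guarantees a weekly draw. Off it, detection depends on whether a clinician orders one. If the true rates are equal, the group that is tested more often will show more events.

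The effect falls on the signal where the protocol itself expresses uncertainty. The Anidulafungin section reports LFT abnormalities of unclear clinical significance, and the dose rationale mentions isolated hepatic events without established causality. A chi-square result on unequally detected events could be read as drug toxicity when it reflects only the testing schedule.

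**Working it through.** **Inputs from the protocol.** There are 100 patients randomised 3:1, so 100 × 3/4 = 75 and 100 × 1/4 = 25. The Sample Size paragraph expects 25% of the surveillance arm to test positive and 19 to receive anidulafungin; 75 × 0.25 = 18.75, which rounds to 19, so its figure is reproduced. That leaves 75 − 19 = 56 surveillance patients untreated. Treatment lasts at least 14 and at most 28 days. The test is two-sided at 5%.

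**Scheduled repeat LFT sets.** On drug there are 14/7 = 2 to 28/7 = 4. In standard care there are 0, or 1 if empiric therapy starts.

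**Assumptions, not in the protocol.** The true rate of an LFT abnormality is 20% in both groups. It lasts w = 1 or 2 weeks. Routine care tests LFTs in a fraction r of weeks, independently from week to week. A weekly scheduled test finds every such abnormality. The single draw at the start of empiric therapy is ignored.

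**Recorded rate off drug** = 0.20 × (1 − (1 − r)^w).

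| r | Off drug, w = 1 | Off drug, w = 2 | On drug |
|---|---|---|---|
| 30% | 6% | 10.2% | 20% |
| 50% | 10% | 15% | 20% |
| 80% | 16% | 19.2% | 20% |
| 100% | 20% | 20% | 20% |

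With w = 1, the spurious difference between drug recipients and standard care is 14, 10, 4 and 0 percentage points.

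**All randomised patients, w = 1.** Preemptive-arm rate = (19/75) × 20% + (56/75) × off-drug rate.

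- r = 30%: 5.07 + 4.48 = 9.5%, against 6%; difference 3.5 points
- r = 50%: 5.07 + 7.47 = 12.5%, against 10%; difference 2.5 points
- r = 80%: 5.07 + 11.95 = 17.0%, against 16%; difference 1.0 point
- r = 100%: 20% against 20%; difference 0

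This counts the 19 as tested weekly throughout. They also have time off drug before the positive test, so the differences are if anything too large.

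**Effect on the chi-square test.** This is an exact binomial enumeration of the uncorrected two-sided 5% test, 19 recipients against 25 standard-care patients, with equal true rates and a fraction q of control abnormalities detected (q = r when w = 1).

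| q | Rejection, true rate 20% | Range, true rates 10% to 40% |
|---|---|---|
| 1 | 4.7% | 4.4% to 5.3% |
| 0.75 | 7.8% | 5.9% to 9.9% |
| 0.50 | 17.1% | 9.8% to 28.0% |
| 0.25 | 37.1% | 16.9% to 65.6% |

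For q of 0.75 or lower, nearly all rejections are against the drug. At a 20% true rate and q = 0.50, 17.0 of the 17.1 points are.

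**The case against.** The strongest reply is that the biased comparison is never actually specified. The Safety paragraph restricts the set to patients given study drug, all of whom follow the same weekly schedule. A comparison inside that set, for example by APACHE II stratum, would carry no schedule imbalance. This stands as a limit on the point: it applies to a comparison with standard care, which the synopsis aim states but the Safety paragraph leaves without a comparator. A reader might infer that the bias arises whatever groups are compared; the text does not support that.

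A reader might also infer that these procedures happen only on anidulafungin, or that an excess on drug is built in. Neither follows. Baseline LFTs and examinations apply to everyone, and an LFT set is listed at the start of empiric therapy. Routine tests count for safety, AEs are recorded weekly in all subjects, and the weekly invasive fungal infection assessment covers vital signs, symptoms and routine laboratory results. If routine care tests LFTs at least weekly, the LFT part of the bias largely vanishes. But baseline and starting values cannot show later change, the protocol neither states nor requires a routine frequency, and a weekly AE record cannot capture an abnormality that was never tested for.

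The trial is also a preliminary feasibility study, the bias runs against the drug, and AE tabulation is often left to an analysis plan. This lowers the stakes. However, the route by which a finding was detected has to be captured at data collection, so the CRF must provide for it.

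**Conclusion.** The point holds as a risk of detection bias in an AE comparison of anidulafungin, or of the preemptive arm, with standard care. It chiefly concerns LFT abnormalities. A similar risk exists for examination findings, but nothing in the protocol allows it to be sized.

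Under the one-week, 20% assumptions the spurious difference is 0 to 14 points for recipients against standard care, and 0 to 3.5 points if all randomised patients are compared. A two-week abnormality narrows the first range to 0 to 9.8 points. Where the truth lies within these ranges depends on routine LFT frequency, which the protocol does not give. The undefined comparator is a linked defect and needs settling in the same edit. The issue should be corrected because safety is a primary endpoint and the change is cheap; it does not undermine the trial as a whole.

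**What to change.** In Assessment of Safety and in the Safety paragraph of the statistical section:

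- Name the groups in the AE comparison, and reconcile the dosed-only safety set with the aim of comparing against current practice.
- On the AE form, record whether each laboratory or examination finding was detected only at a protocol-scheduled assessment, and whether a routine-care test was also done that week.
- Show the between-group comparison twice: with all AEs, and without those detected only at protocol-scheduled LFTs or examinations.
- Report the rates of scheduled-LFT abnormalities descriptively for the anidulafungin group, with no p-value against standard care.

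Both versions are needed because neither is clean. On drug, the weekly AE record is itself taken at the scheduled examination. The Diagnostic Tests section can be read as placing study LFTs in the medical record, so they may replace draws that clinicians would otherwise have ordered. Dropping scheduled findings alone could then undercount hepatic events on drug and reverse the bias.

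The cost is one or two CRF fields, some protocol wording and a second tabulation.
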